## Secondary outcome measures

The GAD-7 [28] is a 7-item scale that measures symptoms of anxiety over the last 2 weeks. Items are scored from 0 to 3 where a total score ranges from 0 to 21 and cut-off scores for mild, moderate and severe anxiety symptoms are 5, 10, and 15 respectively.

The PQSI [29] is a 19-item scale that measures sleep quality and disturbances over the past month. Items generate seven “component” scores: subjective sleep quality, sleep latency, sleep duration, habitual sleep efficiency, sleep disturbances, use of sleeping medication, and daytime dysfunction. Total scores range from 0 to 21 where higher scores indicate worse sleep quality. A cutoff score of 5 is also recommended to distinguish good and poor sleep quality with a good sensitivity of 89.6% and specificity of 86.5%.

The MSPSS [30] is a 12-item scale that measures the perceived availability and adequacy of emotional and instrumental social support using a 7-point Likert scale ranging between 1 “very strongly disagree” and 7 “very strongly agree.” Total scores range from 12 to 84 where higher scores indicate higher levels of perceived support. The MSPSS has demonstrated strong internal consistency (Cronbach’s *α* = 0.87–0.94) and test–retest reliability (*r* = 0.73) among adults.

The PSI-SF [31] is a 36-item self-report measure of parenting stress. It includes three subscales: Parental Distress (PD; e.g., “I feel trapped by my responsibilities as a parent”, “I feel lonely and without friends”), Parent-Child Dysfunctional Interaction (PCDI; e.g., “Sometimes I feel my child doesn’t like me and doesn’t want to be close to me”, “When I do things for my child I get the feeling that my efforts are not appreciated” ), and Difficult Child (DC; e.g., “My child makes more demands on me than most children”, “My child gets upset easily over the smallest thing”). Each subscale consists of 12 items rated from 1 (strongly disagree) to 5 (strongly agree), with subscales scores ranging from 12 to 60. A Total score is calculated by summing the three subscales scores, ranging from 36 to 180. Scores of 90 or above may indicate a clinical level of stress.

The BCRS [32] is a 14-item self-report measure of co-parenting and consists of 7 subscales: co-parenting agreement, co-parenting closeness, exposure to conflict, co-parenting support, co-parenting undermining, endorse partner parenting, and division of labor. Each subscale involves questions including 7 options ranging from 0 (never) to 6 (very often) or 0 (not true of us) to 6 (very true of us). Lower scores in the subscales of exposure to conflict and co-parenting undermining indicate more positive co-parenting as does higher scores in the remaining five subscales.

The DDST [33] is a scale of developmental assessment covering the ages from birth to 6 years. It is made up of 105 items grouped into four sectors including gross motor, fine motor-adaptive, language, and personal-social. Each item is represented by a bar that spans the ages at which 25%, 50%, 75%, and 90% of typically developing children in the standardization sample passed that item. Items that over 90% of children should be able to accomplish which are not successfully completed are considered as a delay and items where the age line passes through the 75–90% section of the bar that are not completed are scored as caution. The results are categorized into 3 types: normal, abnormal (two or more delays), and questionable (two cautions or one delay).

## Sample size and statistical analysis

Based on a previous trial, Chinese pregnant women with depressive symptoms who received CBT delivered face-to-face showed significantly lower rates of postpartum depression than those who received standard antenatal care (22.2% vs 47.3%, *P* = 0.001) [25]. We estimate that a sample size of at least 178 (89 per group, assuming 20% loss to follow-up) is required to detect a 25% reduction in depression symptoms at 6 weeks postpartum on based on a 90% power to detect differences between groups and a two-sided significance level of 0.05. Considering the possible decreased efficacy due to CBT delivered by internet rather than face-to-face, we aim to recruit 300 participants in this study.

All data will be extracted from the security server of the main center and incorporated in a single Microsoft Excel database through the computer system. The original data will be verified by researchers before analyzed and non-conforming data will be excluded with certain reasons listed. For analysis, descriptive statistics of continuous variables will be represented as means and standard deviations or medians and inter quartile ranges. Categorical variables will be expressed as frequencies with proportions. Differences of continuous variables with normal distribution between groups will be tested by Student’s *t*-test, whereas Mann-Whitney *U* test will be applied to variables with skewed distribution. Categorical variables will be tested by chi-square test. Demographic and medical characteristics at baseline will be analyzed for whether they are equivalent between two groups; otherwise, a subgroup analysis will be performed for adjusting confounding factors. Main analyses will be conducted using intention-to-treat (ITT) model, in which all participants will be included based on random allocation regardless of study completion. For outcomes collected at multiple time points, repeated measures design using generalized estimating equation (GEE) models will be conducted to fit outcomes that are measured at each time point, so that all the participants might contribute to the analyses, even if there were missing data at some of the follow-up points. In addition, statistical analysis of the baseline characteristics of those who remain in the study and those who are lost to follow-up will also be conducted to explore whether there is differential drop out. All statistical analyses will be performed using the R software (version 4.0.2) or other statistical software packages if necessary. Differences will be considered significant if the two-sided p value is less than 0.05.

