### Study setting

Pregnant women will be recruited through obstetric clinics at the International Peace Maternity and Child Health Hospital in Shanghai China and other four cooperative medical centers from different regions in China including (1) Hunan Maternal and Child Health Care Hospital in Changsha, Hunan; (2) Women’s Hospital affiliated with Zhejiang University School of Medicine in Hangzhou, Zhejiang Province; (3) Hanghzhou Women’s Hospital in Hangzhou, Zhejiang Province; and (4) Shaoxing Maternity and Child Health Care Hospital in Shaoxing, Zhejiang Province.

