#### Participant screening, recruitment, and enrolment

All pregnant women will be assessed with EPDS by a trained research assistant during their standard antenatal visit between 28 and 34 weeks gestation. Those with an EPDS > 9 will be introduced to the study and provided with a detailed study explanation. Eligible women agreeing to participate will complete informed consent procedures and will be financially compensated when they finished the trial. Following the completion of a baseline questionnaire, women will be randomized to either the control group (standard care for women with antenatal depressive symptoms) or the intervention group (standard care for women with antenatal depressive symptoms plus access to iCBT).

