## Primary outcome measure

The primary outcome is prevalence of depression at 6 weeks postpartum using the PHQ-9, which is a 9-item self-report measurement used to assess depressive symptoms over the last 2 weeks [27]. Each item is scored from 0 (not at all) to 3 (nearly every day) for a total score ranging from 0 to 27. Scores of ≥ 5, ≥ 10, and ≥ 15 represent mild, moderate, and severe levels of depressive symptoms respectively. Psychometric properties and sensitivity to change are well documented [38]. We will re-administer the PHQ-9 at 12, 24, and 52 weeks postpartum to evaluate the longer-term treatment effect of iCBT and the prevention of new cases of depression.

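### Confounder adjustment is made to depend on a baseline equivalence check, and the remedy named, a subgroup analysis, does not adjust the overall effect

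*Protocol article*

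**What the plan says.** All of the analysis text is in the protocol article under Sample size and statistical analysis.

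- **Trigger:** "Demographic and medical characteristics at baseline will be analyzed for whether they are equivalent between two groups". No variables, equivalence margin or separate threshold are given. The only threshold in the section is the general one: "Differences will be considered significant if the two-sided p value is less than 0.05".
- **Consequence if the check fails:** "otherwise, a subgroup analysis will be performed for adjusting confounding factors".
- **Main analysis set:** the next sentence places the main analyses on an intention-to-treat basis, keeping every randomised woman.
- **Tests:** "Categorical variables will be tested by chi-square test"; for continuous variables, Student's t-test or Mann-Whitney U. None of these takes a covariate. GEE models are named for outcomes measured repeatedly, with no covariates listed.

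Elsewhere in the article:

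- **Primary outcome measure:** "The primary outcome is prevalence of depression at 6 weeks postpartum using the PHQ-9", so the outcome is binary.
- **Participant screening, recruitment, and enrolment:** the screening step reads "All pregnant women will be assessed with EPDS by a trained research assistant during their standard antenatal visit between 28 and 34 weeks gestation". Entry requires a score above 9, so every participant has an EPDS score before randomisation. Table 2 schedules no baseline PHQ-9.
- **Study setting:** the lead hospital plus "other four cooperative medical centers from different regions in China", five centres in all.
- **Randomization and blinding:** allocation is 1:1, in computer-generated blocks, through a central web-based system. No stratification factor is mentioned.

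**The concern.** The rule has three faults, all in what is written rather than in what is left out.

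1. With allocation by a central system, any baseline difference between the arms is chance. A test of that difference cannot tell the analyst whether adjustment is needed. Whether adjustment matters depends on how strongly a variable predicts the outcome, not on its baseline p-value.
2. Failing to find a difference does not show equivalence, and no margin is stated against which equivalence could be judged.
3. A subgroup analysis estimates the effect separately within strata. Unless those estimates are pooled, it gives no adjusted overall effect and leaves the main comparison as it was.

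At stake is which additional analyses are run and reported. No variables or strata are named, so this would be settled by the baseline data. In the one situation that the rule is meant for, a chance imbalance in a variable that predicts depression, the named remedy does not correct the main result.

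**Working it through.** **Inputs.** From the article: event rates 47.3% and 22.2%, two-sided alpha 0.05, power 90%, loss to follow-up 20%, target 300. Assumed, because the article gives no figure: the number k of baseline characteristics tested, their independence, use of the general 0.05 threshold for the baseline check, and the strength of the link between EPDS and the outcome.

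**The plan's own figure.** Unpooled two-proportion formula: (1.960 + 1.282)² × (0.473 × 0.527 + 0.222 × 0.778) / 0.251² ≈ 70.4, so 71 per arm. Then 71 / 0.80 = 88.75, so 89 per arm and 178 in total. This reproduces the stated minimum, which is not in dispute. With the target of 300, completers number 300 × 0.80 / 2 = 120 per arm. That figure is used below.

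**How often chance sets off the rule.** P(at least one flagged) = 1 − 0.95^k.

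| k (assumed) | Probability |
|---|---|
| 5 | 23% |
| 10 | 40% |
| 15 | 54% |
| 20 | 64% |

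Correlated characteristics would change these values.

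**What happens when a prognostic variable is imbalanced.** Simulation under no treatment effect: 120 per arm, event rate 47.3%, 8,000 trials per setting. It has one baseline covariate, with an assumed log-odds per SD. An imbalanced trial is one where that covariate differs between the arms at p < 0.05, which is about 5% of trials.

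| Log-odds per SD | Unadjusted type I error, all trials | Unadjusted, imbalanced trials | Adjusted, imbalanced trials |
|---|---|---|---|
| 0.5 | 4.5% | 7% | 6% |
| 1.0 | 5.2% | 16% | 5% |
| 1.5 | 4.6% | 17% | 5% |

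So the unadjusted test is valid over all randomisations. Given a visible imbalance in a strong predictor it can mislead, and prespecified adjustment removes the problem. The imbalanced columns rest on roughly 400 trials each (5% of 8,000), so they are approximate.

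**Precision gained by adjusting for EPDS.** Simulation: 120 per arm, 47.3% versus an assumed 31%, 1,500 trials per setting, chi-square against logistic regression with EPDS.

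| Correlation (assumed) | Power, chi-square | Power, adjusted |
|---|---|---|
| 0.3 | 76% | 77% |
| 0.4 | 76% | 80% |
| 0.5 | 77% | 82% |

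Before rounding, the last two rows are 75.7% to 79.9% and 76.7% to 82.5%, gains of 4.2 and 5.8 points. No figure was derived for centre.

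**The case against.** The strongest defence is that the sentence is loosely worded and does little damage. Four parts of it stand.

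- **The subgroup result does not displace the main comparison.** A reader might infer that it does, and then quote the loss of power when 120 per arm become 60: from 98.6% to 83% at 47.3% versus 22.2%, or from 66% to 39% for an assumed 15-point difference. The article does not support this. Its next sentence keeps all randomised women in the main analyses, so the plain reading is that the subgroup analysis is additional. What role its result would play is not stated.
- **The primary test is not invalid.** A reader might infer an inflated type I error. Over all randomisations it stays near 5%; the higher figures apply only given imbalance in a strong predictor.
- **The plan cannot be said to ignore EPDS and centre throughout.** The t, Mann-Whitney and chi-square tests take no covariates. For GEE the article is merely silent, as it is on stratification by centre, and a covariate list is commonly left to an analysis plan. PHQ-9 is also measured repeatedly, so GEE rather than chi-square may be intended for the 6-week comparison.
- **A stratified analysis with pooled estimates, such as Mantel-Haenszel, would adjust.** The authors may have meant that, given the stated purpose, but the text names a subgroup analysis and mentions no pooling.

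The gain from EPDS also depends on an assumed correlation, and restricting entry to scores above 9 tends to weaken it. None of this rescues the sentence itself. An analysis plan could add detail, but it would have to contradict this rule, not complete it.

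**Conclusion.** The point holds in limited form. The article fixes a data-dependent trigger and names a method that does not do what it is said to do. The trigger would be met by chance in roughly a quarter to two thirds of properly randomised trials for 5 to 20 characteristics, given independence and a 0.05 threshold. The consequences are extra analyses chosen from the data, no real correction when a prognostic variable is imbalanced, and some lost precision. They do not include a biased or invalid intention-to-treat comparison. The precision at stake is modest, about 1 to 6 percentage points of power for assumed correlations of 0.3 to 0.5. The rule should be corrected, but it does not by itself put the primary conclusion in doubt.

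**What to change.** - Delete the baseline-equivalence trigger and the conditional subgroup rule.
- Describe baseline characteristics by arm, without using p-values to choose analyses.
- Prespecify that the 6-week primary comparison adjusts for screening EPDS score and centre whatever the observed balance. Either logistic regression reported as a standardised risk difference, or the GEE model already named, would serve.
- Keep the unadjusted chi-square test as a sensitivity analysis.
- Use subgroup analyses only for prespecified tests of effect modification.

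This is a change of wording plus slightly more analysis work. Screening EPDS and centre are known for every participant, so no new data are needed. The Trial status section reports 203 women randomised with data collection continuing; the change should be recorded before outcomes are examined by arm.

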## Risk management strategies

Several strategies will be implemented to mitigate potential risk. First, potential participants who endorse self-harm on the EPDS or PHQ-9 undergo a suicide risk assessment. Those who score positive for suicide ideation will be referred to the emergency department or a mental health specialist for immediate assessment. As discussed in the consent form to ensure safety, the emergency department or a mental health specialist will be contacted on the participant’s behalf if necessary. Considering the intervention is a non-pharmacological treatment, adverse effects due to the intervention are negligible. However, severe adverse events including suicidal behaviors or deaths will be recorded in case report form and reported in the future published manuscript. Participants are allowed to leave the study at any time based on their personal willingness. Research assistants are required to complete the withdrawal report form in detail.

## Ethics and dissemination

Ethical approval was obtained from the institutional review board of International Peace Maternity and Child Health Hospital (GKLW2020-25). All substantial amendments will be notified to the research ethics committee and to the regulatory authority. Results from this trial will be disseminated to the academic community through conference presentations and the publication of peer-reviewed manuscripts. Results will further be made available to participants, health care providers, and the general public. For further access to participant-level dataset or statistical code, please contact the corresponding author.

## Data management

Baseline data including demographic characteristics and pregnancy complications will be collected by the research assistant using an online questionnaire based on previous research conducted by our team [6]. The name of each participant will be replaced with a computer-generated serial number for identification. All data will be stored on a secure server at the International Peace Maternity and Child Health Hospital and will be password-protected. Only the principal investigator will have access to any identifiable data, and the data will be analyzed by a biostatistician blinded to group allocation. De-identified data will be made available on reasonable request if compliant with the receipt of ethical approval from both the sending and receiving institutional ethics review boards.

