### Study objectives

The primary objective of this study is to evaluate the effect of iCBT on reducing depression symptoms among pregnant women in their third trimester with the aim of preventing depression across the postpartum period assessed using the Patient Health Questionnaire 9-item scale (PHQ-9) [27]. The secondary objectives are to evaluate the effect of iCBT on (1) anxiety using the Generalized Anxiety Disorder (GAD-7) [28], (2) sleep quality using the Pittsburgh Sleep Quality Index (PSQI) [29], (3) social support using the Multidimensional Scale of Perceived Social Support (MSPSS) [30], (4) parenting stress using Parenting Stress Index-Short Form (PSI-SF) [31], (5) co-parenting relationship using the Brief Co-parenting Relationship Scale (BCRS) [32], and (6) infant development using the Denver Development Screen Test (DDST) [33].

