## Outcomes

Primary and secondary outcomes were chosen based on previous CBT studies and other postpartum depression prevention trials. The aim is to include outcomes that will evaluate effect of the iCBT intervention on depression symptoms that started before childbirth and prevent the development of depression across the first year postpartum. Refer to Table 2 for the schedule of study assessments measured at each follow-up time point to 12 months postpartum.

**Table 2 Tab2:** Outcome measurement and timing of data collection

Data collection		Time of measurement					
Content	Assessment criteria	Baseline	Postpartum				
			6 weeks	3 months	6 months	9 months	1 year
Demographics	Questionnaire form	**×**					
Primary outcomes							
Depression	PHQ-9		**×**				
Secondary outcomes							
Depression	PHQ-9			**×**	**×**		**×**
Anxiety	GAD-7		**×**	**×**	**×**		**×**
Sleep Quality	PSQI			**×**	**×**		**×**
Social Support	MSPSS				**×**		
Parenting satisfaction	PSI-SF					**×**	
Co-parenting relationship	BCRS					**×**	
Infant development	DDST			**×**	**×**		**×**

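### Table 2 schedules no GAD-7, PSQI or MSPSS before randomisation, so these secondary comparisons stay unbiased but lose precision and cannot be checked for imbalance or dropout on their own scales

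*Protocol article*

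**What the plan says.** Table 2 of the protocol article, titled "Outcome measurement and timing of data collection", has a baseline column. The only row marked in it is "Demographics Questionnaire form". The row "Sleep Quality PSQI" is first marked at 3 months, then at 6 months and 1 year. The row "Social Support MSPSS" is marked once, at 6 months. GAD-7 is first marked at 6 weeks, then at 3 months, 6 months and 1 year.

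Data management describes what is gathered at entry: "Baseline data including demographic characteristics and pregnancy complications will be collected by the research assistant using an online questionnaire". The enrolment section gives the order of events: "Following the completion of a baseline questionnaire, women will be randomized". The one symptom score clearly placed before randomisation is the screening EPDS: "All pregnant women will be assessed with EPDS by a trained research assistant during their standard antenatal visit between 28 and 34 weeks gestation".

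The statistical section plans t-tests or Mann-Whitney tests for continuous variables and GEE for outcomes measured repeatedly. It also plans a check of demographic and medical characteristics between arms, and a baseline comparison of women who stay with women who are lost.

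**The concern.** Anxiety, sleep quality and social support are named secondary objectives. Each can be measured in the third trimester, unlike parenting stress, co-parenting and infant development, which need a born child. The means of collecting them is already in place, because women fill in an online form before they are randomised.

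Three things are given up.

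- **Precision.** Stable differences between women stay in the error term. The abstract says the sample has sufficient power for primary and secondary outcomes, but the only calculation shown is for depression at 6 weeks.
- **The imbalance check.** The planned baseline comparison cannot cover entry levels of anxiety, sleep or support.
- **The dropout check.** The plan assumes 20% loss and intends to look for differential dropout. It cannot ask whether loss depends on these scales at entry. MSPSS is worst placed: with a single reading, no earlier score can inform a missing one.

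This cannot be left to an analysis plan, since no analysis can adjust for a score that was not collected.

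**Working it through.** **The plan's own figure.** The protocol gives no precision or power figure for the secondary outcomes. Its one calculation is for depression: 22.2% vs 47.3%, 90% power, two-sided 0.05, 20% loss, 89 per group. With the unpooled normal approximation:

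n = (1.960 + 1.282)² × (0.473 × 0.527 + 0.222 × 0.778) / 0.251² = 70.4, rounded up to 71 per arm; 71 / 0.80 = 88.75, rounded up to 89 per arm, 178 in total.

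This reproduces and is not affected by the present point.

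**Inputs for the secondary outcomes.**
- Target 300, so 150 per arm; after 20% loss, 120 per arm (Sample size section).
- 203 already randomised (Trial status), so at most 300 − 203 = 97 to come.
- Baseline-to-follow-up correlation ρ: not in the documents. Assumed range 0.3 to 0.6.

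**Unadjusted comparison.** In SD units, SE = √(2/120) = 0.129. The difference detectable with 80% power is (1.960 + 0.842) × 0.129 = 0.362 SD.

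**If every woman had a baseline score.** The variance is multiplied by 1 − ρ².

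| ρ | Variance cut | SE (SD) | Detectable at 80% power (SD) | Power at 0.362 SD |
|---|---|---|---|---|
| 0.3 | 9% | 0.123 | 0.345 | 84% |
| 0.5 | 25% | 0.112 | 0.313 | 90% |
| 0.6 | 36% | 0.103 | 0.289 | 94% |

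**What can still be gained.** If at most 97 of 300 women have a baseline score and a missing indicator is used for the rest, the average cut is about (97/300) × ρ². This takes dropout to be similar in earlier and later women.

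- ρ = 0.3: 0.323 × 0.09 = 2.9%; 1/0.971 = 1.03.
- ρ = 0.5: 0.323 × 0.25 = 8.1%; 1/0.919 = 1.09.
- ρ = 0.6: 0.323 × 0.36 = 11.6%; 1/0.884 = 1.13.

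At ρ = 0.5 the detectable difference moves from 0.362 to 0.362 × √0.919 = 0.347 SD.

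**Is the unadjusted comparison biased?** A simulation under no effect, with ρ = 0.5, 120 per arm and 20,000 runs, gave a mean unadjusted difference of 0.000 SD and a type I error of 5.1%, against 4.9% with adjustment. Only the spread differed: 0.129 vs 0.112 SD.

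**Items to add.** From the outcome descriptions: GAD-7 7, PSQI 19, MSPSS 12; 7 + 19 + 12 = 38.

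**The case against.** **The comparison is valid without a baseline.** A reader might infer that effects on these scales cannot be told apart from differences the women brought with them. The documents do not support that. Allocation is 1:1 through a central web-based system after baseline data are collected. Differences at entry are therefore chance only, are already covered by the standard error, and leave the error rate at about 5%. This objection stands in full.

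**The baseline form may hold more than the article shows.** The Data management sentence gives examples rather than a closed list, and it refers to a questionnaire from earlier work that is not shown. Table 2's baseline column also omits pregnancy complications and the screening EPDS, both of which are collected. The risk section mentions self-harm answers on the EPDS or PHQ-9 among potential participants, although Table 2 marks no baseline PHQ-9 either. This lowers certainty. Still, nowhere does the article place GAD-7, PSQI or MSPSS before randomisation, and Table 2 has a baseline column in which their cells are blank.

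**Covariates may be specified elsewhere.** The GEE models could include the screening EPDS, and the article does not say whether they do. So one cannot say that every outcome will be compared as a raw score. The EPDS could help in part, most plausibly for anxiety. It is a depression score, restricted here to values above 9, and does not replace prior sleep or perceived support.

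**The gain is small and may come late.** A reader might take the 25% variance cut at ρ = 0.5 to mean that a third more women are being forgone (1/0.75 = 1.33). That would need a baseline score from all 300. Data collection is due to end in September 2022 with follow-up to one year, so enrolment would have to end around mid-2021. The change may reach few women. This stands and limits the size of the point.

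**Conclusion.** The point holds as a modest loss of precision and of diagnostic checks on three secondary outcomes, caused by a schedule choice that was cheap to avoid. It is not a bias, and it does not touch the primary outcome's sample size.

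Full baseline collection would have cut variance by 9 to 36%. What remains within reach is about 3 to 12%, or 8% at a correlation of 0.5, which is worth roughly 9% more women. It is less if enrolment is close to its end. These figures rest on an assumed correlation of 0.3 to 0.6, which the documents neither give nor secure: follow-up crosses childbirth and runs up to a year beyond it. They also rest on reading the blank baseline cells in Table 2 as meaning that the scales are not collected. If the unseen questionnaire does contain them, the remedy reduces to correcting Table 2 and using the scores.

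**What to change.** 1. For women still to be enrolled, add GAD-7, PSQI and MSPSS to the existing pre-randomisation online form, and mark them in the baseline column of Table 2. If any is already collected, say so there.
2. Include each baseline score as a covariate in the model for that outcome: GEE for GAD-7 and PSQI, a regression for the single MSPSS reading. Use a missing indicator for women randomised earlier. This is sound in a randomised comparison, because here missingness is set by date of entry and so does not depend on the arm.
3. For all women, also adjust for the screening EPDS, already collected, and describe it as a partial substitute.
4. Add the new scores to the planned comparison of women retained and women lost.

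The cost is 38 items answered once, a few more minutes at enrolment, and a short addition to the analysis text. The gain is partial. If enrolment has closed, only the EPDS adjustment remains, and the report should state that no baseline exists for these three scales.
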